## **APPENDIX O      Dissatisfaction Scale**

To what extent do you feel dissatisfied with your current weight loss progress?

## **APPENDIX P      Economics of Obesity**

### **PART I:**

We are now going to ask you some questions about your income. This is an important part of this study, so we appreciate your cooperation and accuracy. Remember that everything you tell us will remain confidential and NO information that would identify you will be used in any data analysis.

Do you currently receive income from wages or salary?

- 1)      YES
- 2)      NO

If No, then skip to Part IV. If yes, then continue to PART II.

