### Economics of obesity

There is a large literature in economics that finds that heavier individuals are less likely to be employed and, when employed, tend to earn less (see e.g. Cawley, 2004; Averett, 2011). (This disadvantage is greater for women than men). Some studies have been conducted that seek to measure whether this relationship is causal; that is, whether being heavier lowers wages. These studies rely on natural experiments, which have some advantages but also have the disadvantage that they are not based on a randomized controlled trial. In this study we will also seek whether weight loss is followed by improvements in employment and wages or salary. In addition, we seek to measure the mechanism of any such changes: specifically, whether the weight loss results in fewer days missed due to poor health, or less discrimination in the workplace on the basis of the subject's weight. Collectively, these results will greatly improve our understanding of whether weight lowers employment and wages, and if so, whether it is due to poor health or employer discrimination.

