#### 6.3.15 Economics of Obesity

This questionnaire assesses whether weight loss is followed by improvements in employment and wages or salary. It will be completed by Participants at Baseline, Month 6 and Month 12. See Appendix P.

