## PART III

Including any paid or unpaid overtime, how many hours PER WEEK do you usually work in all your jobs?

(Please enter the actual number of hours you work per week)

In the past month, how frequently have you had trouble performing the duties of your work because of ill health or disability?

- (1) Often; (2) Sometimes; (3) Rarely; (4) Never.

In the past month, how many days did you miss work because of physical illness or injury, or a mental or emotional problem such as stress or depression?

(Please enter actual number of days missed)

In the past month, how frequently have you been discriminated against in the workplace (for example, not hired for a job, not given a promotion or opportunity, fired, or paid less) because of your weight?

(1) Often; (2) Sometimes; (3) Rarely; (4) Never.

How frequently in the past month have you been treated with less courtesy or respect at work because of your weight?

(1) Often; (2) Sometimes; (3) Rarely; (4) Never.

End survey.

PART IV:

In the past month, have you been looking for paid work?

1) Yes; 2) No.

If answered Yes, then ask the next two questions; otherwise (if answered No) then end the survey.

In the past month, how frequently have you had trouble looking for or getting paid work because of ill health or disability?

(1) Often; (2) Sometimes; (3) Rarely; (4) Never;

In the past month, how frequently have you been discriminated against in the labor market (for example, not hired for a job or offered less pay) because of your weight?

(1) Often; (2) Sometimes; (3) Rarely; (4) Never;

End survey.

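### The Appendix P earnings form admits respondents to its work questions by receipt of wages or salary, so self-employed participants who draw no wage cannot be told apart from people who do not work

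*Protocol*

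**What the plan says.** Appendix P is completed at Baseline, Month 6 and Month 12 (Section 6.3.15). Part I asks one thing: "Do you currently receive income from wages or salary". The routing follows: "If No, then skip to Part IV. If yes, then continue to PART II".

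Part II asks for the most recent pay, whether it is before or after tax, and the period it covers. Part III holds the work items. They include hours ("Including any paid or unpaid overtime, how many hours PER WEEK do you usually work in all your jobs"), trouble performing duties, absence ("In the past month, how many days did you miss work because of physical illness or injury") and weight discrimination ("In the past month, how frequently have you been discriminated against in the workplace"), with a further item on courtesy and respect at work.

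Part IV first asks whether the respondent has been seeking paid work in the past month. Its rule is: "If answered Yes, then ask the next two questions; otherwise (if answered No) then end the survey". The two further items cover health-related difficulty in finding work and weight discrimination in the labour market.

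On purpose, Section 6.3.15 states: "This questionnaire assesses whether weight loss is followed by improvements in employment and wages or salary". The Economics of obesity part of Section 2 gives the same aim and adds a mechanism: fewer days lost to poor health, or less weight discrimination at work. Secondary Objective 13 (Section 3) concerns financial outcomes for participants in general and is not restricted to wage earners.

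**The concern.** The gate tests a type of income, but it controls access to items about work of any kind. A participant living from their own business can truthfully answer No and be treated as having nothing to report on hours, absence or ability to do the job.

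Two things are at stake. First, employment is a named outcome, and for this group the form cannot show whether it is present or has changed. Second, the mechanism questions are missing for people who work but draw no wage, at every visit where that is so. Coding rules can wait for an analysis plan. They cannot restore answers that were never requested.

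**Working it through.** No sample size, power or error-rate formula applies. The check traces each kind of respondent through the form as printed.

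| Respondent | Part I | Parts II and III | Part IV |
|---|---|---|---|
| Wage or salary earner | Yes | all items | not reached |
| Self-employed, also draws a wage or holds a wage job | Yes | all items | not reached |
| Self-employed, no wage, not seeking paid work | No | none | first item only |
| Not working, not seeking work | No | none | first item only |
| Self-employed, no wage, seeking paid work | No | none | all three items |
| Not working, seeking work | No | none | all three items |

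Rows three and four follow the same path and leave the same answers, so the form has no means of separating them. Rows five and six also share one path.

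**Is the information held elsewhere?** I found no item in the protocol that records employment status. The screening medical history (Section 6.1) lists no occupation question. The SF-36 in Appendix B asks whether health limits work or other daily activities, not whether the person is employed.

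**Change over the three visits.**
- Wage job to self-employment without a wage: Yes then No, the same as losing work.
- The reverse move: No then Yes, the same as gaining work.
- Self-employed without a wage throughout: No at all three visits. No false change arises, but Part III is missing each time.
- Starting or stopping such self-employment from or to no work: No at both visits, so a real change does not show in the Part I answer.

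**Scale.** The protocol gives no employment or self-employment figures. With the planned 400 participants (Section 11.3), each percentage point who are self-employed and draw no wage is 400 x 0.01 = 4 people. Purely as an assumption, 5% to 20% would be 400 x 0.05 = 20 to 400 x 0.20 = 80 people. That range counts people who would miss Parts II and III at one visit. It does not count people who change status, and nothing in the protocol allows that number to be estimated.

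**The case against.** The strongest defence is that the routing works as written and matches a deliberate scope. Section 2 sets out to learn "whether weight loss is followed by improvements in employment and wages or salary", and its mechanism is poor health or discrimination by an employer. Most examples in the Part III discrimination item (being hired, promoted, dismissed or underpaid) presuppose an employer. Omitting business income and employer discrimination for the self-employed could therefore be intended.

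That carries weight for Part II and for the discrimination items. It does not explain why hours, trouble with duties and days missed are withheld from people who work. Nor does it explain why employment, named alongside wages or salary, is read from a question about wages or salary alone.

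A reader might infer more than the form supports in four ways:
- That these participants **are counted as not employed**. The protocol states no coding rule. It supports only that they are indistinguishable from people without work.
- That they **give no work or discrimination data at all**. Those seeking paid work answer the two further Part IV items, one of them on labour-market discrimination.
- That **all self-employed participants are lost**. Anyone who draws a wage from their own company, or also holds a wage job, can answer Yes, and the hours item then covers all their jobs.
- That **the understatement of the employment rate can be quantified**. Any such figure needs outside employment shares. It would also describe a level at one visit, whereas the aim concerns change after weight loss, and a person who is self-employed throughout adds no false change.

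**Conclusion.** The point stands in a limited form. Part I selects on receipt of wages or salary when the later items require selection on being in work. Self-employed participants who draw no wage and answer No are not asked about pay, weekly hours, trouble with duties, days missed or workplace discrimination, and they cannot be separated from people who do not work. Moves between wage work and self-employment would resemble losses or gains of employment.

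The conclusion rests on the printed routing and on the absence of another employment item in the protocol. It assumes that a self-employed person without a wage reads the Part I question literally. The number affected, and the number of false changes, cannot be derived from the protocol. Only secondary Objective 13, one of 24 secondary objectives, is touched. The primary endpoints and the sample size are not. Severity: minor.

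**What to change.** Reword the Part I question to ask about any current paid work, with four options: wages or salary; self-employed or own business; both; none. Route as follows:
- **Wages or salary:** Part II, then Part III.
- **Self-employed or own business:** a short business-income item, then Part III.
- **Both:** Part II and the business-income item, then Part III.
- **None:** Part IV, unchanged.

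Add a not-applicable option to the employer-discrimination items in Part III. Define employment for the analysis as any of the first three options.

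The business-income item is needed. Sending the self-employed straight to Part III would still leave their income unasked, although Objective 13 is about financial outcomes. Without the not-applicable option they would face questions that assume an employer.

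The cost is one reworded question, one added item, an extra response option and a new skip rule in the electronic questionnaire (Section 12). Under Section 16.10 the change needs sponsor agreement and ethics committee approval before use. Forms completed earlier keep the old coding, so the change date must be recorded and those forms flagged. Comparisons that span the change need care, because an apparent change in employment could come from the new question.

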## PART II

[Please show the next three questions simultaneously on the screen, so the respondent sees that they can choose to report their pay by week, fortnight, month, or year and either before or after tax.]

What was the amount of your most recent pay? It will help to answer this question if you can refer to your last pay-slip. Please enter amount in dollars.

And is that before tax or after tax is taken out?

- 1) Before tax is taken out
- 2) After tax

And what period does that cover?

- 1) Week
- 2) Fortnight
- 3) Month
- 4) Year

Continue to Part III.

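### The earnings form takes one recent pay but hours over all jobs, so it cannot give total earnings or a matched wage for participants with more than one job

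*Protocol*

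**What the plan says.** Objective 13 (Protocol, Section 3) is to find out whether weight loss leads to better financial outcomes. The introduction, under Economics of obesity, states the aim: "In this study we will also seek whether weight loss is followed by improvements in employment and wages or salary". Section 6.3.15 names the same outcome for the Appendix P questionnaire and schedules it at Baseline, Month 6 and Month 12.

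In Appendix P, Part II the pay item asks "What was the amount of your most recent pay" and suggests the last pay-slip as the source. Two follow-up items record the basis of that amount: "And is that before tax or after tax is taken out" and "And what period does that cover". A screen instruction says respondents should see that "they can choose to report their pay by week, fortnight, month, or year and either before or after tax".

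Part III then asks "Including any paid or unpaid overtime, how many hours PER WEEK do you usually work in all your jobs".

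**The concern.** The two items have different scope. Pay is one amount, with a single pay-slip as the suggested source. Hours are summed over every job. Nothing in Part II prompts a respondent with two jobs to add the pays together or to say which job the amount comes from, and nothing in Part III separates main-job hours from the rest.

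The outcome is change within a person over three visits. Taking on or dropping a second job is one of the ways in which a participant's earnings can change, and it is the case that the form handles worst. The gain may go unrecorded, or the job behind the most recent pay may differ from one visit to the next. The number of jobs is not collected, so an analyst could not tell which participants are affected.

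**Working it through.** The protocol states no figure for the wage outcome, so there is nothing to reproduce. The check sets the items side by side and then sizes the possible error under stated assumptions.

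**Scope of each item**

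| Item | Jobs covered | Time reference |
|---|---|---|
| Pay (Part II) | The job behind the most recent pay | Most recent, with the period recorded |
| Hours (Part III) | All jobs, with paid and unpaid overtime | Usual week |

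With one job, the two rows refer to the same job. With two or more they need not, and no other item on the form supplies the missing pay or the missing split of hours.

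**Size for a person with several jobs.** Let s be the share of all-job hours that the reported pay covers, and assume equal hourly rates across jobs. Recorded pay ÷ true total pay = s. Pay divided by all-job hours is also s times the true hourly rate. So earnings, and an hourly wage if one were derived, are both too low by 1 − s:

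- s = 0.9: 10% too low
- s = 0.7: 30% too low
- s = 0.5: 50% too low

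**Average over respondents.** With a share m holding several jobs, the mean understatement is m × (1 − s). The documents give neither quantity. Over an assumed m of 3% to 15% and s of 0.5 to 0.9, it runs from 0.03 × 0.1 = 0.3% to 0.15 × 0.5 = 7.5%.

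**Effect on change.** Take a participant with 38 hours in one job at Baseline who adds 8 hours in a second job by Month 6, at the same hourly rate (the hours are assumed). True weekly earnings rise by 8/38 = 21%. On a weekly basis the form may record:

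- no change, if the amount given is the first job's pay; the hourly figure then changes by 38/46 − 1 = −17.4%
- 8/38 − 1 = −79%, if the second job paid most recently and only that amount is given
- +21%, if the respondent adds the two pays unprompted

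With 4 or 12 added hours in place of 8, the hourly figure in the first case changes by 38/42 − 1 = −9.5% or 38/50 − 1 = −24.0%. The direction of error in recorded earnings therefore depends on what the respondent chooses to report. If the jobs, and the job reported, stay the same at every visit, s is constant and cancels from a relative change.

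**Tax basis.** At an assumed average tax rate t, a switch from before-tax to after-tax reporting moves the raw amount by −t, and the reverse switch by 1/(1 − t) − 1. For t of 10% to 30% this is −10% to −30%, or +11% to +43%. The basis is recorded at each completion, so such a switch can be seen in the data.

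**The case against.** The strongest reply is that the protocol never defines the Objective 13 outcome as pay divided by hours. Hourly wages appear only in the introduction's account of patterns of thought, a different sub-study, and there as a result from the literature. Hours can stand alone as a measure of labour supply, and how a wage variable is derived is normally left to an analysis plan, which is not at hand. That is right, and a reader who infers from the mismatch that the wage outcome as a whole is measured wrongly goes beyond the documents. What survives does not need an hourly wage: total earnings are also missing for people with several jobs, and no analysis plan can restore an amount that was not collected.

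A reader might also infer that a change of tax basis between visits would pass unnoticed as a change in earnings. The documents do not support this. Basis and period are recorded every time, so a switch biases the result only if the analysis ignores the item. Exact conversion is not possible from the form, so some precision is lost, but the screen instruction shows that the choice was deliberate, and insisting on before-tax amounts could cost accuracy among people who know only their take-home pay.

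Finally, the self-employed are routed past the pay and hours items. That looks like a gap, but the stated outcome is wages or salary, and the routing question in Part I matches it. Including self-employment income would extend the outcome; its absence does not contradict the protocol.

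The reply is also right that the job-scope problem is confined to people with several jobs and largely cancels from relative change when their situation is stable.

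**Conclusion.** The point holds in a limited form. For participants with more than one job, or whose number of jobs changes between the three visits, Appendix P cannot give total earnings or a wage consistent with the recorded hours, although wages or salary is a stated outcome. Respondents who hold one job throughout do not have this job-scope mismatch.

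The size cannot be established from the documents. The share with several jobs, the split of their hours and their pay rates are not given, so the percentages above rest on assumed ranges and on equal hourly rates, and serve only as illustration. Objective 13 is one of 24 secondary objectives, and for wage earners the missed-days, work-difficulty and discrimination items do not depend on the pay item. The primary endpoints and the sample size are unaffected. It is a cheap improvement to one instrument.

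**What to change.** Give the pay and hours items the same job scope. Either ask in Part II for total usual pay from all jobs over the stated period, or keep a main-job pay item and add main-job hours beside it. Use the same wording at Baseline, Month 6 and Month 12.

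Keep the tax-basis item. Ask respondents to report on the same basis as at their previous visit where they can, or take the recorded basis into account when change is analysed.

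The cost is one reworded or added question in a questionnaire that Section 12 already has completed electronically. Participants who have answered the existing item at Baseline need care, because a new wording at Months 6 and 12 would itself break comparability within a person. For them, keep the existing item alongside the new one, or report their results with the one-job limit stated as a limitation. Converting existing data to weekly pay avoids the hours mismatch but does not bring back the missing second-job pay.

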## PART III

Including any paid or unpaid overtime, how many hours PER WEEK do you usually work in all your jobs?

(Please enter the actual number of hours you work per week)

In the past month, how frequently have you had trouble performing the duties of your work because of ill health or disability?

- (1) Often; (2) Sometimes; (3) Rarely; (4) Never.

In the past month, how many days did you miss work because of physical illness or injury, or a mental or emotional problem such as stress or depression?

(Please enter actual number of days missed)

In the past month, how frequently have you been discriminated against in the workplace (for example, not hired for a job, not given a promotion or opportunity, fired, or paid less) because of your weight?

(1) Often; (2) Sometimes; (3) Rarely; (4) Never.

How frequently in the past month have you been treated with less courtesy or respect at work because of your weight?

(1) Often; (2) Sometimes; (3) Rarely; (4) Never.

End survey.

PART IV:

In the past month, have you been looking for paid work?

1) Yes; 2) No.

If answered Yes, then ask the next two questions; otherwise (if answered No) then end the survey.

In the past month, how frequently have you had trouble looking for or getting paid work because of ill health or disability?

(1) Often; (2) Sometimes; (3) Rarely; (4) Never;

In the past month, how frequently have you been discriminated against in the labor market (for example, not hired for a job or offered less pay) because of your weight?

(1) Often; (2) Sometimes; (3) Rarely; (4) Never;

End survey.

## APPENDIX Q Participant Food Diary

**FOOD & ACTIVITY DIARY**

Trial name: FBCx and GinST 15

Participant ID: \_\_\_\_\_

Visit: \_\_\_\_\_

© [name], Accredited Practising Dietitian. Adapted by [name], Accredited Practising Dietitian The Boden Institute

### PLEASE READ THROUGH THE FOLLOWING PAGES BEFORE BEGINNING YOUR FOOD DIARY

Please keep a record of everything you eat and drink for 3 days (2 working days and 1 weekend day) prior to your appointment. Please include **ALL** foods and drinks consumed at home and outside the home e.g. at work, friend's houses, restaurants etc. Remember that it is normal to sometimes eat or drink things that you may prefer nobody else knows about. However, for our study we need the most accurate records as possible, so it is very important that you do not avoid writing something down because you think it may be a less desirable option or change what you eat and drink because you are keeping a record. We appreciate that at times completing this diary accurately will take you some time and you may find the process tiresome. We wish to take this opportunity to sincerely **thank you** for your contribution to our research.

2

### HOW TO RECORD YOUR FOOD INTAKE

- Please write clearly and legibly, use a blue or black ball point pen.
- Start each day on a **new page** and write the **date** at the top.
- Each time you eat or drink something, record the **time** and **place**. It is best to record at the time of eating or drinking **NOT** from memory at the end of the day. The diary was designed to be a convenient size for a handbag or pocket, so please carry it with you. If you forget to take it with you, try writing on another piece of paper at the time of eating rather than trying to remember later on.

3

